### Refinement of Tasks and Outcomes for Future Clinical Use

To reduce the number of tasks and outcomes, a variable selection procedure will be implemented. First, objective turning outcomes for each task will be ranked according to their (1) AUC in differentiating people with mTBI from healthy control subjects, (2) correlation with functional performance in the civilian-relevant task, (3) correlation with functional performance in the military-relevant task, and (4) ratio of mean effect of rehabilitation over minimum detectable change. Outcome–task combinations will then be ordered according to the sum of their ranks across these four categories, where a lower total is better. The outcome, and associated task, with the lowest total sum will be identified and put forward in future applications and clinical training tools. Additionally, a civilian-specific task/outcome combination will be identified by summing the ranks, but excluding the rank corresponding to the correlation with functional performance in the military-relevant task. A military-specific task/outcome combination will be identified similarly, but summing all ranks except the correlation with functional performance during the civilian-specific task.

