#### Primary Outcome Measures—Diagnostic Accuracy

The primary outcome measures will be obtained through a series of clinical turning tasks (Table 1). Each participant will complete three prescribed clinical turning assessments in the laboratory while being measured with wearable sensors. The prescribed tests will involve a 1-min walk test between two lines on the ground marked 6 m apart (1MW), a modified Illinois Agility Test (mIAT) (65, 66), and a custom clinical turning course (CCTC) designed to mimic turns performed in daily life (21) (Figure 1). All participants will perform one block of turning tasks. Each block will consist of one 1MW, one mIAT, and one CCTC performed with no additional cognitive task, and one 1MW, one mIAT, and one CCTC performed with a simultaneous cognitive overlay. The cognitive overlay for the 1MW and the mIAT involves an 8-digit grid coordinate memorization task. The overlay for the CCTC involves monitoring and responding to keywords in a custom-developed simulated radio chatter task (28). A subset of participants will complete a second block of turning tasks to establish test–retest reliability and minimum detectable change.

**Table 1 T1:** Primary outcomes from objective turning tasks in phase 1.

	**Description**	**Purpose**

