**Cognitive DT outcomes**		
Cognitive-task accuracy	Assesses the percentage of cognitive task responses that are correct in dual-task conditions	To compare whether cognitive performance when turning is impaired in people with mTBI
Number of correct responses per second	Assesses the overall number of correct responses, divided by the overall time in seconds	

* *These measures will involve assessment of both the mean and the variability (i.e., standard deviation)*.

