#### Sample Size

Sample size calculation and power analysis were based on Hedge's *g* effect sizes determined through preliminary data on turning in people with mTBI (21); we observed a range of Hedge's *g* effect sizes of −1.09 to −1.32 between the peak lumbar turn velocity of healthy controls and people with mTBI and residual symptoms when performing 90° turns. With 50 civilian participants per group and the midrange effect size from our preliminary work, we will have 90% power to detect differences in peak lumbar turning velocity between healthy controls and people with mTBI with a two-tailed 0.01 significance level if we observe at least 65% of the effect size we observed previously (*g* = −1.20). For the second goal, the power analysis was based on the correlation between clinic-based peak turning velocity and the duration of walking bouts, a common measure of daily ambulatory function, exhibited during daily, unmonitored activities at home (Pearson ρ = 0.362, data obtained from DoD #W81XWH-15-1-0620). With 140 planned participants (100 civilian participants and 40 active-duty participants), we will have 97% power to detect a correlation between the lumbar turning velocity measured in the clinic and daily function with a two-tailed 0.01 significance level if we observe the same effect size. Power calculations were performed in G^*^Power 3.1.9.2 (68).

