Similar heterogeneity exists in the timeline of care and symptomology for individuals with mTBI. Based on recent evidence that active rehabilitation can be initiated within several weeks after mTBI and may yield greater gains than a traditional wait-and-see approach (96–99), the recent Clinical Practice Guidelines for Physical Therapy Evaluation and Treatment after mTBI state time since injury should not independently drive decisions about rehabilitative care (100). As a consequence, an ideal RTD assessment should be based on the occupational or situational demands one will face and should be applicable to individuals at various times since injury with diverse symptomology. This study will address whether the proposed tests are suitable as a universal RTD assessment, regardless of time since injury or symptom presentation. Yet, it is possible that performance will vary based on these factors. We will probe these relationships and adjust our planned analyses as appropriate pending the distributions of our final sample.

Because of the large sample size, multisite design, and inclusion of both civilian and active duty military populations, the results of this study are generalizable and can be rapidly implemented into clinical practice. To translate the results of this study into clinical environments, we will (1) develop standardized administration manuals and scoring sheets for each turning task/outcome selected for clinical use and (2) make recommendations to integrate these training and administration materials into DoD professional development and training courses for rehabilitation specialists. To facilitate widespread implementation, we will publish all analysis algorithms and clinical protocols on freely available, open-access repositories. Finally, we plan to seek future funds to translate the analysis algorithms and protocols to ubiquitous mobile technologies (e.g., cell phones) that do not rely on relatively expensive and specialized commercial technologies.

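### The rank-sum puts forward one outcome–task combination from 30 to 60 candidates on point estimates alone, so the winner may not be distinguishable from its close competitors

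*Protocol article*

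**What the plan says.** The section Refinement of Tasks and Outcomes for Future Clinical Use ranks each outcome–task combination on four criteria. Combinations are then "ordered according to the sum of their ranks across these four categories, where a lower total is better". The decision follows directly: "The outcome, and associated task, with the lowest total sum will be identified and put forward in future applications and clinical training tools". Two further selections, one civilian and one military, each drop one criterion and repeat the sum.

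The field of candidates comes from the section Primary Outcome Measures—Diagnostic Accuracy and from Table 1:
- Tasks: "Each participant will complete three prescribed clinical turning assessments in the laboratory while being measured with wearable sensors".
- Conditions: each block has the three tasks without a cognitive task, and then "one 1MW, one mIAT, and one CCTC performed with a simultaneous cognitive overlay".
- Outcomes: for the starred rows of Table 1, "These measures will involve assessment of both the mean and the variability (i.e., standard deviation" applies.

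Uncertainty is planned elsewhere. Statistical Analysis gives bootstrap intervals for each AUC and Holm-adjusted comparisons of turning measures with clinical assessments. Secondary Statistical Analyses marks outcomes with an ICC above 0.7. The Phase 2 outcome section interprets ratios above 1. None of these is a condition or an input in the rank-sum. The Discussion says that "the results of this study are generalizable and can be rapidly implemented into clinical practice".

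**The concern.** A rank keeps the order of two estimates and discards both the gap between them and the precision of each. A trivial difference in AUC and a large one can each cost one rank. The responsiveness criterion rests on 40 people, and its denominator comes from a test–retest subset whose size is not given, yet it counts as much as the other three criteria.

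The sample size section powers tests against no effect. It does not address telling one candidate from another. The planned AUC comparisons set turning measures against clinical assessments, not against each other. Nothing in the stated rule would therefore show whether the winner stands apart from the next few candidates.

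The combination that comes first among many noisy estimates also tends to have estimates that are too favourable. Its AUC and correlations will overstate how it performs in new people. At stake is the measure carried into manuals, scoring sheets and training recommendations.

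**Working it through.** **1. The plan's own figures.** The article states "With 50 civilian participants per group and the midrange effect size from our preliminary work, we will have 90% power" at a "two-tailed 0.01 significance level if we observe at least 65% of the effect size we observed previously".
- Goal 1: effect 0.65 × 1.20 = 0.78, so the non-centrality is 0.78 × √(50/2) = 3.90. Normal approximation: Φ(3.90 − 2.576) = 90.7%. Noncentral t: 89.6%. The stated 90% reproduces.
- Goal 2: atanh(0.362) × √(140 − 3) = 0.379 × 11.70 = 4.44, and Φ(4.44 − 2.576) = 96.9%. The stated 97% reproduces.

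The article gives no figure for the selection step.

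**2. Number of candidates.** Table 1 has four starred turning measures, each as mean and SD, and two unstarred: 4 × 2 + 2 = 10. Over three tasks this is 30; over both conditions it is 60. Counting the two cognitive dual-task outcomes adds 2 × 3 = 6, for 36 or 66. With four criteria, 30 to 60 candidates mean 120 to 240 ranked estimates.

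**3. Precision of a single estimate.**
- AUC: a standardised difference of 0.78 gives Φ(0.78/√2) = 0.709. With 50 per group the standard error (Hanley–McNeil) is 0.052. For two candidates whose errors correlate 0.5 (assumed), the standard error of the difference is 0.052 × √(2 × 0.5) = 0.052. A gap of about 1.96 × 0.052 = 0.10 is needed to separate them.
- Correlation: the 95% interval around 0.362 is 0.21 to 0.50 with n = 140, and 0.18 to 0.52 with n = 100.

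**4. Stability of the choice.** This was a simulation of 4,000 studies per scenario. The following are assumptions, not figures from the article:
- mean true values: d 0.6, r 0.30, change-to-MDC ratio 0.6;
- true quality correlated 0.5 across criteria, unless stated otherwise;
- error correlation between candidates 0.3 or 0.7 (0.5 in the unrelated-criteria and leader rows);
- standard errors: √(2/50 + 0.36/200) = 0.204 for d; 1/√97 = 0.102 and 1/√137 = 0.085 for the Fisher-transformed correlations (civilian task with 100 people, military task with 140); 0.7/√40 = 0.111 for the change in MDC units, with 8% error in the MDC.

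| Assumed true spread (SD of d, r, ratio) | Truly best chosen, 30 / 60 candidates | Same winner in a repeat, 30 / 60 |
|---|---|---|
| None | 3–4% / 1–2% | 3–4% / about 2% |
| Small (0.1, 0.05, 0.1) | 34–45% / 29–40% | 20–31% / 15–25% |
| Moderate (0.2, 0.10, 0.2) | 56–66% / 52–63% | 41–53% / 37–50% |
| Moderate, criteria unrelated | 45% / 40% | 31% / 26% |
| Large (0.35, 0.15, 0.35) | 69–77% / 66–75% | 56–68% / 53–64% |
| Leader ahead of the next best by 0.2, 0.06, 0.15 | 95% / 96% | 91% / 92% |
| Leader ahead by 0.4, 0.12, 0.3 | over 99% | over 99% |

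Pure chance would pick the best in 1/30 = 3.3% or 1/60 = 1.7%. Under small to moderate spread (criteria correlated) the chosen candidate is among the true top five in 68–98% of studies.

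A second simulation with other assumptions (d mean 0.5, SD 0.2; r mean 0.25, SD 0.10; standardised change mean 0.30, SD 0.15) gave the same winner in 27–52% of pairs of studies and the truly best candidate in 43–66%. That range varies only the number of candidates and the error correlation. It does not cover the unknown spread.

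**The case against.** The rule is prespecified and transparent, and it does far better than a random draw. A reader might infer from the instability that the recommended test is largely chance. The check does not support that. Under small to moderate spread the truly best candidate is chosen in 29–66% of studies, against 1.7–3.3% by chance. Only near-equal candidates bring the choice close to chance, and then a wrong pick costs little. No loss in AUC, correlation or responsiveness from choosing a non-best candidate has been calculated.

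The article also reports preliminary effects of −1.09 to −1.32 for peak lumbar velocity, so a strong candidate on the AUC criterion is plausible. That concerns one criterion and one kind of turn, and gives neither the values of the other candidates nor the spread. It does not show a leader on all four criteria.

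A reader might also conclude that the plan has no measure of uncertainty at all, or that the winner passes unexamined into training. Neither is right. AUC intervals and ICCs are planned and would be visible beside the winner. The Discussion makes adoption conditional, expects that one measure may not meet every criterion, and speaks of making recommendations for training courses.

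Finally, a full protocol or SAP may contain a stability analysis that a journal article omits. That limits the point to the decision rule as stated. The article does fix that rule, and the rule uses point estimates only.

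**Conclusion.** The point holds in a limited form. The stated rule selects one combination, plus a civilian and a military one, from 30 to 60 candidates without carrying sampling uncertainty into the ranking. The winner may not be distinguishable from close competitors, and its AUC and correlations taken from the same data are optimistic. The direction of that optimism follows from the selection; its size was not calculated.

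The size of the instability is conditional. A repeat study names the same winner in about 15–53% of cases under an assumed small to moderate spread, and in over 90% with a clear leader on all four criteria. Over all the scenarios the figure runs from 2–4% to above 91%, and the article gives nothing that fixes where in that range the study will lie. This is a worthwhile and inexpensive improvement to a stated rule. It does not show that the rule picks the wrong test.

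**What to change.** Keep the prespecified rank-sum and add a bootstrap of the whole procedure:

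1. Resample people within each Phase 1 group (civilians with mTBI, civilian controls, active-duty controls) and within Phase 2. Recompute all four criteria, including the minimum detectable change, then the ranks and the sums.
2. For the overall, civilian and military selections, report each combination's selection frequency and a rank interval.
3. For the selected measure, report optimism-corrected AUC and correlations. In each resample, select the winner, take its performance there minus its performance in the full data, and subtract the average difference from the reported value.
4. When recommending the winner, state which combinations are not distinguishable from it.

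No new data are needed; the cost is some computing. The downside is that the recommendation may read as a short list instead of a single test. If there is a clear leader, the same output will show it.

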## Discussion

The functional deficits after mTBI can be subtle and are often overlooked in routine clinical assessments. Overt balance and mobility deficits during clinical tests typically resolve within 3 to 5 days after mTBI (83), but persistent, subtle abnormalities have been detected using sophisticated instrumentation and analysis techniques (53, 84–91). Increasing the difficulty or complexity of a task, such as adding a simultaneous cognitive DT, can also reveal subtle abnormalities; numerous studies describe the ability of DT measures to detect subtle, residual deficits from mTBI that may not be detected by traditional single domain assessment strategies (28, 49, 50, 92). Tests of physical function, such as the FGA and HiMAT, assess global performance during these complex tasks, but lack objectivity and nuanced measurement scales (12) that limit the tests' sensitivities (93, 94). However, recent advances in wearable technologies have enabled objective, sensitive assessments of subtle motor deficits during common clinical tests (8, 9, 95). By leveraging wearable sensors to quantify turning, an ecologically relevant and complex task, we hope to improve clinical decision-making after mTBI.

Clinical feasibility and ceiling effects in high-performing individuals are two main challenges in designing ecologically relevant assessments for RTD decisions. In tackling these challenges, we considered the following principles—the RTD assessment must be limited in time and equipment and easily administered; the clinically feasible assessment should, on its face, be ecologically relevant; performance on the assessment should be directly associated with performance in real-world tasks; and there should be no ceiling caused by the measurement technique (25). These principles led to the adaptation of three clinically feasible turning tasks that can each be administered with little additional training. While these tasks directly quantify the speed of turning, an ecologically relevant action performed hundreds of times per day (45), the tasks themselves are constrained based on clinical feasibility; they do not incorporate some of the complexities of the real world. Thus, the ability of outcomes from these turning tasks to predict performance on more specialized tasks (our CAT and SUP) is critical to the ecological relevance. Finally, while these turning tasks are rather simple compared to a simulated battle drill, wearable sensors facilitate continuous, objective outcome measures without an arbitrary ceiling due to the method of measurement.

If we find the DT turning performance can improve diagnostic accuracy of standard clinical assessments, is associated with functional performance in ecologically relevant tasks, and is responsive to rehabilitation, the results of this study will motivate rapid adoption of DT turning assessments in mTBI rehabilitation and RTD decisions. However, we anticipate that a single outcome measure may not satisfy all of these criteria. By instrumenting various body segments with wearable inertial sensors, we will simultaneously capture multiple outcome measures, each quantifying distinct aspects of movement (Table 1), for each task. Current clinical assessments of physical function lack this feature; they provide only one global score. However, clinical assessments with too many outcomes can become unguided. Our procedure to refine the selection of tasks and outcomes will rank outcomes based on their individual attributes (e.g., diagnostic accuracy, predictive capacity, sensitivity to change), as well as their overall combined attributes. These rankings will then guide the selection of tasks and outcomes that are ultimately recommended for clinical implementation.

Occupational demands and physical capabilities vary widely between and within civilians and military populations. Thus, adequate performance on the proposed turning tasks may be viewed as the bare minimum standard for RTD decisions. Because of the vast heterogeneity in occupational demands and physical capabilities both within and outside of the military, the current study is not designed to determine how performance varies by these factors. However, we anticipate addressing the extent to which performance differs between general civilian and military populations. If military populations perform differently (e.g., turn faster), it supports the use of population-adjusted normative ranges. Yet, even population adjusted normative ranges fail to address the variability within each subset due to occupation or physical health. Accordingly, the results of this study may be seen as a stepping stone for more individualized, and perhaps more complex, RTD assessments based on specific occupational duties.

Similar heterogeneity exists in the timeline of care and symptomology for individuals with mTBI. Based on recent evidence that active rehabilitation can be initiated within several weeks after mTBI and may yield greater gains than a traditional wait-and-see approach (96–99), the recent Clinical Practice Guidelines for Physical Therapy Evaluation and Treatment after mTBI state time since injury should not independently drive decisions about rehabilitative care (100). As a consequence, an ideal RTD assessment should be based on the occupational or situational demands one will face and should be applicable to individuals at various times since injury with diverse symptomology. This study will address whether the proposed tests are suitable as a universal RTD assessment, regardless of time since injury or symptom presentation. Yet, it is possible that performance will vary based on these factors. We will probe these relationships and adjust our planned analyses as appropriate pending the distributions of our final sample.

Because of the large sample size, multisite design, and inclusion of both civilian and active duty military populations, the results of this study are generalizable and can be rapidly implemented into clinical practice. To translate the results of this study into clinical environments, we will (1) develop standardized administration manuals and scoring sheets for each turning task/outcome selected for clinical use and (2) make recommendations to integrate these training and administration materials into DoD professional development and training courses for rehabilitation specialists. To facilitate widespread implementation, we will publish all analysis algorithms and clinical protocols on freely available, open-access repositories. Finally, we plan to seek future funds to translate the analysis algorithms and protocols to ubiquitous mobile technologies (e.g., cell phones) that do not rely on relatively expensive and specialized commercial technologies.

## Ethics Statement

The studies involving human participants were reviewed and approved by Oregon Health and Science University IRB, University of Utah IRB, Allina Health IRB, U.S. Army Medical Research and Materiel Command (USAMRMC), Office of Research Protections (ORP), Human Research Protection Office (HRPO). The patients/participants provided their written informed consent to participate in this study.
